#### Tracking and retention

At the 2-month visit, researchers will explain to participants the importance of maintaining up-to-date contact information, provide a prepaid mailer with a change of address/phone number form, and ask for names and contact information for three additional adults (e.g., nearby relatives, friends) who may be contacted in the event participants become difficult to reach over the course of the study. Participants will receive the study team’s phone, email, and web contact information to communicate any scheduling changes or changes in contact information. To maximize participant retention, we will use our partnership with EHS to track participants who enroll in the study through EHS records, including home addresses and forwarding addresses if families relocate. To minimize travel or other burden on study participants, we will align in-person data collection procedures with the regular EHS site or home visit for EHS participants. As incentives for participation in the survey, participants will receive $30 for visit 1, $40 for visit 2, $50 for visit 3, and $60 for visit 4, the amount increasing over time to encourage continued participation. Prior obesity trials with children had an average retention rate of 86% [69]. Feeding data participants will receive $50 each provision of feeding data. Each dyadic interview participant will receive $30.

### Phase 2 - enhanced intervention development and pilot testing

This phase involves two steps: developing intervention components that can be added to EHS’ existing nutrition education program and testing the enhanced intervention.

#### Step 1: intervention development

To develop the intervention components on feeding styles and practices and multiple caregivers, we will engage in a process of information gathering, focus groups, intervention refinement, and cognitive debriefing interviews. We will identify existing evidence-based interventions and “best practices” from the literature on nutrition, early childhood obesity prevention, and culturally grounded interventions for low-income families that inform intervention development. The study team will gather information on infant feeding and childhood obesity interventions, such as the Greenlight NOURISH Project, [70] the Soothe/Sleep project, [71] and projects in the Arikpo et al. [72] systematic review of randomized controlled trials of infant feeding interventions. It will synthesize this information, along with any relevant information from the current EHS nutrition education program and Phase 1 study findings. Because our pilot work revealed many EHS-enrolled mothers were also enrolled in the Special Supplemental Nutrition Program for Women, Infants, and Children (WIC), [47] we will also synthesize relevant WIC nutrition education material to ensure intervention components are consistent with WIC messages.

Once we develop drafts of the intervention components, we will conduct 6 focus groups of 10 people each (3 with mothers and other caregivers, 3 with EHS staff) to gather feedback and any additional ideas on what should be included. For nonprobability samples, 80% of themes can be identified within two to three focus groups and 90% within three to six focus groups [73]. The study team will facilitate the groups and take notes to document key discussion points and themes. We will ask for participant feedback on EHS’s current nutrition education, relevant findings from Phase 1, and components of existing interventions relevant to infant feeding styles and practices and multiple caregiver feeding. We will prompt discussion about the material and how each may fit with the needs of low-income families, encouraging participants to suggest other optimal intervention components for further development. We will also ask about infant feeding: challenges in multiple caregiver contexts, personal and environmental facilitators and barriers to infant feeding, and motivators for improving infant feeding (see Additional file 4 for interview guide). Focus groups are ideal as they allow participants to build on each other’s ideas [74].

Focus groups will be audio-recorded and analyzed using template and matrix analysis, a rapid analytic technique [75]. The study team will listen to audio recordings and insert data, including illustrative excerpts from the interviews, in the templates. Next, a matrix (focus group × domain) will be created, and data from each template will be inserted into the matrix. This approach facilitates identifying patterns across groups. We will create two separate matrices (one from groups with mothers and caregivers and one from groups with EHS staff) from which we will create two separate lists of identified content for the intervention components. The Community Advisory Board will review the content identified for the components and make recommendations. Ultimately, the study team will use the recommendations to develop the components.

After the focus groups, intervention refinement working group meetings and cognitive debriefing interviews will be held to finalize the intervention components. We will create an intervention refinement working group of 5–7 people: academics, EHS-enrolled mothers, and EHS staff. Findings from Phase 1 and the focus groups will help inform the intervention components; however, we expect to develop at least two intervention components, both of which may be characterized by educational sessions (60–90 min each), text messages, and printed materials. The working group will develop the intervention components and suggest refinements to them, which will then be incorporated in an iterative fashion and brought back to the group, [76] which may need to meet 2–3 times to revise the components. The study team will incorporate any suggested changes. Before finalizing the intervention components, they will be translated from English to Spanish and back, ensuring both versions are culturally relevant, accessible, and available.

We will then conduct one-time cognitive debriefing interviews with 10 EHS-enrolled mothers. We will interview 3 mothers in English and 3 in Spanish and incorporate their feedback. After revisions are incorporated, we will interview two other mothers in English and 2 in Spanish. In previous work, we found that feedback from 3 to 5 interviews (in any one language) is sufficient. We will interview in the two language groups because components will be in both English and Spanish. In the interview, participants will review the materials for the components, followed by relatively structured questions to assess understanding of the material. The study team will conduct interviews, eliciting information on: 1) appropriateness of language, 2) relevance of material, and 3) unclear, confusing, or misunderstood material [77]. The 75-min, in-person interviews will occur at EHS sites and be audio-recorded. The interviewer will also take notes. Immediately following the interview, the interviewer will listen to the audio recording and use their notes to identify needed revisions [78]. These notes will be compiled, discussed by the study team and CAB members, and incorporated. The results for Step 1 will be validation-ready drafts of the components that will comprise the enhanced intervention.

#### Step 2: pilot testing via a cluster randomized controlled trial (RCT)

To pilot test the enhanced intervention at EHS sites, we will compare the enhanced intervention’s feasibility, acceptability, and preliminary efficacy in improving maternal feeding styles and practices to EHS’ existing intervention. Prior to designing a larger trial, it is imperative to have data on recruitment processes (% eligible, reasons for not participating, recruitment yield), baseline process data (% completion, time range from recruitment to intervention, attendance/sessions completed), baseline survey data, and outcome data including preliminary effect sizes. These data will inform the sample size for a future RCT.

With EHS staff, we will identify two EHS sites and optimal dates/times during their regular monthly site-based group meetings for intervention implementation. Sites will be randomly assigned, via coin toss, to the treatment or control condition. The enhanced intervention will be implemented in a two-month period to align with the implementation of existing nutrition education. We will train an EHS staff person at each treatment site to deliver the enhanced intervention. At the control sites, existing nutrition education will be provided as usual.

Random selection will be used in which 15 mothers from both sites will be selected to participate (30 mothers total, 15 treatment and 15 control). This sample is appropriate for a pilot whose aims are to assess feasibility, acceptability, and preliminary efficacy [79]. EHS staff will recruit EHS-enrolled mothers as part of their regular outreach with program families, using the eligibility criteria for Phase 1.

The research team will observe implementation for fidelity and qualitative debriefing interviews with five EHS staff members, including the implementers, to assess feasibility (e.g., fit with existing programming and program requirements, participant retention) and acceptability (e.g., format and length, cultural relevance). Members of the study team will attend the EHS group meetings to administer brief paper-and-pencil pre- and post-tests to participating mothers; these members will be blinded to the experimental control. At treatment sites pre-tests will be administered immediately prior to intervention implementation, and post-tests will be administered 1 month after the end of implementation. At control sites, the pre- and post-tests will be administered 3 months apart, in alignment with the treatment site data collection.

To determine preliminary efficacy, pre- and post-tests will assess increases in participants’ knowledge and use of responsive feeding styles and recommended feeding practices using the IFSQ and BBNQ; decreases in risky feeding practices using the BBNQ; increases in knowledge of the role of other caregiver feeding practices (based on results from Phase 1); and increases in use of recommended strategies for negotiating infant feeding with other caregivers (based on results from Phase 1 and Step 1 of Phase 2). Measures for the latter two outcomes will be developed by the research team. Post-tests of the treatment group will also assess the enhanced intervention’s acceptability (e.g., format and length), cultural relevance, and overall satisfaction (e.g., “In general, how satisfied were you with the intervention?”).

We will consider the intervention feasible if qualitative analysis of EHS staff feasibility data (observations and debrief interviews) reveals no major concerns and at least 80% of intervention participants are retained at the post-test. We will consider the intervention to be acceptable if at least 80% of participants indicate that they were “satisfied” or “very satisfied” with the intervention. With regard to preliminary efficacy, our goal for the pilot is to determine whether the enhanced intervention positively impacts the proximal outcomes of feeding styles and practices and caregiver context, with the idea that if it does, it will positively impact on the distal outcomes of infant growth and obesity as tested in a future trial. Using quantitative analysis, we will assess pre- to post-test changes in outcomes in the treatment and control conditions, using general linear mixed models and/or permutation tests. We will consider the intervention preliminarily efficacious if the changes trend in the desired direction. The results of Step 2 will be the enhanced intervention and information on the feasibility, acceptability and preliminary efficacy of the enhanced intervention.

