#### Eligibility and recruitment

EHS staff, specifically home-based educators and center-based teachers, will facilitate the recruitment of mothers into the study. These staff members have direct contact with mothers either through weekly home-based visits or center-based daycare services. Prior to the start of recruitment, the study team held trainings with EHS staff in the four counties to provide an orientation to the study, including an overview of CBPR and the academic team’s partnership with EHS, the research aims, and recruitment procedures. During the training, home-based educators and center-based teachers along with EHS leadership decided on aspects of the recruitment procedures. Specifically, the discussion determined how to communicate among EHS staff/ supervisors and the study team when participants were identified.

To create a cohort of 300 mothers and their infants, EHS staff will distribute study flyers with eligibility criteria and study contact information to mothers on their caseload who are pregnant or who have an infant between the ages of 0 to 2 months. When mothers express interest, EHS staff will share the name and age of the child with the study team. Eligible mothers and their infants are enrolled in the study. Mothers must meet the following eligibility criteria: 1) be biologically female, 2) be 18 years of age or older, 3) have a child between ages 0 to 2 months that was born as a singleton, had a normal birth weight (greater than or equal to 5 lbs., 8 oz.), and be enrolled in EHS, 4) speak English or Spanish, and 5) be able to participate in four interviews over 2 years.

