#### Survey measures

Infant weight and length will be measured to produce the two dependent variables: infant growth and obesity. Weight will be measured to the nearest 0.1 kg using calibrated Seca scales. Recumbent length will be measured to the nearest 0.5 cm using standard length rods. We will use the Centers for Disease Control (CDC) and Prevention SAS Macros for the World Health Organization (WHO) growth charts to convert weight and length measures into z-scores. WHO reference standards of gender-specific weight-for-length z-scores at ages 2, 6, 12, and 24 months will be used to evaluate infant growth and obesity.

Infant growth will be calculated as the growth trajectory over the first 24 months of life, using growth curve models of weight-for-length z-scores. We will explore the trajectory with different starting points, using the infant’s birth weight-for-length (reported by mother and converted to z-score) as baseline z-scores.

Obesity at 24 months will be calculated by the child’s body mass index (BMI), the standard clinical measure of obesity in children 2 years and older. We will assess this measure as kilograms of weight per square meter of length, and derive age- and gender-specific BMI percentiles, weight-for-age and BMI-for-age z-scores according to US national standards.

Feeding styles will be measured by the Infant Feeding Style Questionnaire (IFSQ), [56] which has 63 items on infant feeding beliefs and behaviors and 20 additional behavioral items related to solid feeding for children over 6 months of age. The questionnaire captures five feeding styles (i.e., laissez-faire, pressuring, restrictive, responsive, and indulgent) previously validated in a low-income sample of parents of infants and toddlers. Feeding practices will be measured by the 28 items (33 at 12 months) from the Baby Basic Needs Questionnaire (BBNQ) [57] pertaining to feeding, such as whether the child is breastfed exclusively or in combination with formula, when breastfeeding ended (if applicable), whether the child is exclusively formula fed, whether the child is fed solid foods, when solid foods were introduced, and what solid foods and other beverages are fed.

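### The pilot trial takes over the Phase 1 eligibility criteria unadapted: a two-year availability rule that does not fit a 3-month pilot, and an infant age band that leaves the usable IFSQ item set undefined

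*Protocol article*

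**What the plan says.** The section on Step 2 (pilot testing via a cluster randomized controlled trial) states the pilot's eligibility by cross-reference only: "EHS staff will recruit EHS-enrolled mothers as part of their regular outreach with program families, using the eligibility criteria for Phase 1". The criteria are listed under Eligibility and recruitment in Phase 1. The third asks that the mother "have a child between ages 0 to 2 months that was born as a singleton". The fifth asks that she "be able to participate in four interviews over 2 years".

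The pilot's own schedule is much shorter. "The enhanced intervention will be implemented in a two-month period". At the treatment site the pre-test comes immediately before implementation and "post-tests will be administered 1 month after the end of implementation". At the control site "the pre- and post-tests will be administered 3 months apart".

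Preliminary efficacy is judged on pre- to post-test change in feeding styles and practices, using the IFSQ and the BBNQ. Survey measures describes the IFSQ as 63 items on beliefs and behaviors plus "20 additional behavioral items related to solid feeding for children over 6 months of age". It describes the BBNQ as asking, among other things, whether solids are fed, when they were introduced and which are given. It states no minimum age for those questions.

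**The concern.** The Phase 1 criteria were written for a cohort seen four times up to 24 months. The pilot is a different study, and two of the criteria sit badly in it.

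The availability criterion has no counterpart in the pilot's schedule. Step 2 gives the pilot's purpose as supplying recruitment data (percentage eligible, reasons for not participating, yield), process data and preliminary effect sizes for planning a larger trial. A mother who could complete a 3-month pilot but cannot promise two years would be counted as ineligible. The recruitment figures then answer a question that the later trial need not ask. Retention is also exposed: feasibility requires at least 80% of intervention participants at post-test, and mothers screened for a two-year commitment may be easier to keep for 3 months.

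The age criterion interacts with an instrument whose content changes at 6 months. If infants stay below that age, 20 IFSQ items never apply. If some pass it between the tests, the pre-test and post-test are not based on the same items, and a change score mixes a change in behavior with a change in questionnaire.

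**Working it through.** **Inputs** (protocol article)
- Infant age at recruitment, a: 0 to 2 months (Eligibility and recruitment).
- Implementation: 2 months; post-test 1 month after it ends; control-site tests 3 months apart (Step 2).
- IFSQ: 63 core items, plus 20 for children over 6 months (Survey measures).
- Pilot size: 15 mothers per arm; retention threshold 80% (Step 2).
- Lag L from recruitment to pre-test: not fixed. Step 2 lists the time from recruitment to intervention as something to record. I assume 0 to 6 months, and that the age criterion applies at recruitment.

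**The plan's own figures.** Treatment-site interval: 2 + 1 = 3 months, which agrees with the control site. Pilot size: 2 × 15 = 30, as stated.

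**Availability criterion.** Phase 1 has four visits up to 24 months. The pilot has two tests over 3 months. If p is the proportion meeting all the other criteria and q the share of those who cannot commit to two years, the recorded percentage eligible is p × (1 − q) instead of p. The article gives no value for q, so only the direction is known: downward for the percentage eligible and for yield. For retention, 80% of 15 is 12 mothers, and 11 of 15 is 73%, so a single mother can decide whether the threshold is met. Whether criterion 5 would shift retention by that much is unknown.

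**Infant age at the tests.** Age at pre-test = a + L. Age at post-test = a + L + 3.

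| Lag L (months) | Age at pre-test | Age at post-test |
|---|---|---|
| 0 | 0–2 | 3–5 |
| 1 | 1–3 | 4–6 |
| 2 | 2–4 | 5–7 |
| 3 | 3–5 | 6–8 |
| 4 | 4–6 | 7–9 |
| 5 | 5–7 | 8–10 |
| 6 | 6–8 | 9–11 |

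An infant is over 6 months at post-test when L > 3 − a, and at pre-test when L > 6 − a.
- Recruited at 2 months: over 6 months at post-test if L > 1, at pre-test only if L > 4.
- Recruited at birth: over 6 months at post-test if L > 3, at pre-test only if L > 6.

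**Consequence for the items.** With L up to 1 month, no infant is over 6 months at either test, so both tests rest on the same 63 items. An infant crosses the boundary between tests when 3 − a < L ≤ 6 − a, that is, 1 < L ≤ 4 if recruited at 2 months and 3 < L ≤ 6 if recruited at birth. Such an infant has 63 applicable items at pre-test and 63 + 20 = 83 at post-test. A matched change on the 20 items needs a lag of more than 4 months even for the oldest eligible infants.

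**The case against.** The strongest reply is that little is lost. The section on Step 2 names no separate solid-feeding outcome. The over-6-month limit attaches only to the 20 additional IFSQ items, and for a younger infant the 63 core items are the applicable set. The BBNQ carries no stated age limit. The Background names early introduction of solids as a risk practice, and that can be observed at 3 to 5 months. Knowledge and beliefs are assessed as well as use, and these can change before solids begin. All of this stands. A reader might infer that the pilot cannot measure feeding of solids at all, or that 20 of 83 IFSQ items (24%) are lost from its endpoints. The documents support neither, since nothing says those 20 items are pilot endpoints.

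A second reply is that very early enrolment is deliberate: the Background criticizes interventions that begin too late. That also stands. Widening the age band is not an obvious improvement, because a wider band would itself straddle the 6-month boundary, and an age covariate does not make different item sets comparable.

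A third is that the harm to the recruitment figures is unquantified, and that the full protocol may adapt the criterion. The first half is fair: there is no figure for how many mothers the rule would exclude, and it goes too far to say the outputs would describe a two-year cohort. Likewise, a reader might doubt that one site can supply 15 mothers of such young infants, but no site caseloads are given and the doubt cannot be tested. The second half is weaker. The article does not leave pilot eligibility open; it states a rule, and that rule does not fit the pilot's stated schedule.

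**Conclusion.** The point holds in two limited parts.

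First, the availability criterion is wrong for the pilot. Read literally, it asks for two years and four interviews in a study with two tests 3 months apart. It biases the percentage eligible and the yield downward and may raise retention. The amount depends on how many otherwise eligible mothers cannot commit for two years, which the article does not give.

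Second, the carried-over age band leaves the IFSQ comparison undefined. The 20 over-6-month items apply at neither test if the lag is 1 month or less. Above 1 month, some infants may cross 6 months between tests and have 63 items at one test and 83 at the other. This rests on the age criterion being applied at recruitment and on a lag that the article does not fix.

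The 63 core items and the BBNQ questions on whether and when solids are given are unaffected, so the pilot can still assess responsive styles and early introduction of solids.

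**What to change.** State eligibility for the pilot in its own right. Replace the fifth Phase 1 criterion with availability for the pre-test, the sessions and the post-test at 3 months. Keep the 0 to 2 month band if it is intended, and say so.

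State that IFSQ pre- to post-test change is scored on the 63 items common to both tests, whatever the infant's age at post-test, and make no claim about effects on feeding of solids after 6 months. Keep the BBNQ questions on whether and when solids are given.

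The cost is a short eligibility amendment with the matching ethics notification, and no pilot information on the 20 over-6-month IFSQ items. If those items matter for the later trial, its planning will need another source for them.

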The ultimate goal of this study is to reduce disparities in childhood obesity by incorporating healthy feeding styles and practices and multiple caregivers’ perspectives into existing nutrition education programs for low-income families. Our preliminary research with low-income Latina mothers in EHS identified the need for research to better understand and address the role of other caregivers. We showed that multiple caregivers, especially grandmothers, are involved in Latinx infant feeding. Although mothers understand the importance of healthy feeding, they may struggle to implement their knowledge in multiple-caregiver infant feeding contexts, increasing the risk for unhealthy infant growth and early childhood obesity [47]. This study addresses these latter concerns first by conducting a longitudinal study to characterize the caregiver context of infant feeding in low-income families and then by developing and testing a version of EHS nutrition programs enhanced by the incorporation of content addressing healthy feeding styles and practices with multiple caregivers.

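### The pilot assigns a knowledge outcome to the IFSQ and BBNQ, but as described they cover beliefs, behaviours and practices, so knowledge of recommended practices has no described measure

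*Protocol article*

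**What the plan says.** The Step 2 section of the Protocol article lists four preliminary efficacy outcomes for the pilot cluster trial. The first is an increase in "knowledge and use of responsive feeding styles and recommended feeding practices using the IFSQ and BBNQ". The second is a decrease in risky practices, measured with the BBNQ. The third is knowledge about the role of other caregivers' feeding. The fourth is use of strategies for negotiating feeding with other caregivers. On the last two the section adds: "Measures for the latter two outcomes will be developed by the research team". It plans no new measure for the first outcome.

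The instruments are described under Survey measures. The IFSQ is a questionnaire "which has 63 items on infant feeding beliefs and behaviors and 20 additional behavioral items related to solid feeding" for children over six months, and it yields five feeding styles. The BBNQ contributes 28 feeding items (33 at 12 months) that measure feeding practices, "such as whether the child is breastfed exclusively or in combination with formula", when solids began, and which foods and drinks are given.

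The Background separates knowing from doing: "Although mothers understand the importance of healthy feeding, they may struggle to implement their knowledge in multiple-caregiver infant feeding contexts".

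**The concern.** The first outcome joins two constructs, knowledge and use, and assigns both to the same two instruments. Use fits them as described. Knowledge does not fit in the same way: no knowledge items or knowledge score are mentioned for either questionnaire, and the sentence on new measures does not reach this outcome.

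The stake is interpretation. The project starts from the view that mothers may hold the right knowledge and still not manage to apply it. If a shift in practice reports is written up as a gain in knowledge, the pilot will seem to have shown something it did not measure. If practice reports stay flat, the team cannot tell whether the sessions failed to teach the recommendations or whether mothers learned them and could not carry them out. Those two results would call for different revisions before the larger trial that the pilot is meant to inform.

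**Working it through.** No formula applies and the plan gives no figure to reproduce. The check sets the outcome wording in Step 2 beside the instrument descriptions in Survey measures.

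| Part of the first outcome | Instruments named | Described content that could serve it | Covered? |
|---|---|---|---|
| Use of responsive styles | IFSQ | behaviour items | yes |
| Use of recommended practices | BBNQ | practice reports | yes |
| Knowledge of responsive styles | IFSQ | belief items, at most a proxy | in part |
| Knowledge of recommended practices | BBNQ | none described | no |

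**Step 1, item content.** The IFSQ has 63 belief and behaviour items and 20 further behavioural items: 63 + 20 = 83. With 28 BBNQ items the total is 83 + 28 = 111; with the 12-month set of 33 it is 83 + 33 = 116. None of these is described as a knowledge item. The totals count what a summary describes. They are not an inspection of the items, which the article does not reproduce, and they do not prove that no item touches on knowledge.

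**Step 2, newly developed measures.** The sentence on team-developed measures covers the third and fourth outcomes only. The third is itself a knowledge outcome, so the plan builds a dedicated measure for one kind of knowledge and relies on style and practice questionnaires for the other.

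**Step 3, what each instrument can separate.** Take two mothers whose infants are fed in the same way. One knows the recommendation and is not able to follow it; the other does not know it.
- On BBNQ practice reports, as described, they give the same answers, because those items ask what the infant is fed.
- On the IFSQ they can differ, because belief items need not move with behaviour items.

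Reading a BBNQ change as a knowledge change therefore requires practice to track knowledge closely. The Background says that link may fail.

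**Step 4, the efficacy goal.** The opening of Step 2 gives the efficacy aim as improving feeding styles and practices. Its closing part names styles, practices and caregiver context as the proximal outcomes. Knowledge of responsive feeding or of recommended practices is not named in either place, so the goal can be assessed with the instruments listed.

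**The case against.** The strongest reply is that knowledge and use is loose wording for the IFSQ's beliefs and behaviours. On that reading a mother who endorses responsive feeding without practising it can be told apart from one who does neither. The items themselves sit in cited sources and an additional file that are not at hand, and a condensed article need not map items to sub-outcomes. The Background also presents basic understanding as already there and places the difficulty in the multiple-caregiver setting, which the plan addresses with two purpose-built measures.

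Much of this stands. The IFSQ belief items do give partial cover for knowledge of responsive feeding, and the item totals show only how the instruments are described. The plan does not itself say that the pilot must separate general feeding knowledge from use.

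It does not remove the point. The article does more than leave detail out: it assigns a named outcome to named instruments, and its own description of them does not bear that out. The belief argument does not extend to the BBNQ, for which only practice content is described. Nor does the article define a belief-based knowledge score, and believing in an approach differs from knowing what is recommended.

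A reader might go further and infer that knowledge goes wholly unmeasured, that knowing and unknowing mothers would score alike on both instruments, or that the pilot's efficacy assessment fails. The documents do not support this. The belief items work against the first two inferences for responsive feeding, knowledge of the other-caregiver role has its own planned measure, and the efficacy goal does not depend on the missing component.

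**Conclusion.** The mismatch is real and narrow. As the article describes the instruments, knowledge of recommended feeding practices has no measure, and knowledge of responsive feeding has at most a proxy in the IFSQ belief items. Use is covered.

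The consequence is modest: one component of one of four efficacy outcomes, in a pilot of 30 mothers (15 per condition) at two sites, judged on whether changes trend in the desired direction. The goal for styles, practices and caregiver context, the feasibility and acceptability criteria, and any effect sizes for styles and practices are unaffected. What needs preventing is a trend in BBNQ practice reports being reported as a trend in knowledge.

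This rests on the article's summary of the two questionnaires being a fair account of their content. If the full instruments contain items on what is recommended, naming those items in the outcome would settle the point.

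**What to change.** In the efficacy outcomes of Step 2, tie the BBNQ and the IFSQ behaviour items to use, tie the IFSQ belief items to beliefs, and report the two separately. Beliefs should not be folded into use, since that would erase the one distinction the instruments can already make. Then choose one of two edits:

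- Replace knowledge with beliefs in the first outcome. This changes wording only. The pilot then makes no claim about knowledge of recommended practices.
- Keep knowledge, and add a few questions on responsive feeding and recommended practices to the measures the research team is already developing for the other-caregiver outcomes. Give them identically to both arms at pre- and post-test. The cost is a handful of items and a slightly longer paper-and-pencil test.

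The second edit is the one that lets a flat practice result be read as a failure to teach or a failure to apply.
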